## Abstract

**Background:**

The speeding increase and the high prevalence of childhood obesity is a serious problem for Public Health. Community Based Interventions has been developed to combat against the childhood obesity epidemic. However little is known on the efficacy of these programs. Therefore, there is an urgent need to determine the effect of community based intervention on changes in lifestyle and surrogate measures of adiposity.

**Methods/design:**

Parallel intervention study including two thousand 2249 children aged 8 to 10 years ( 4^th^ and 5^th^ grade of elementary school) from 4 Spanish towns. The THAO-Child Health Program, a community based intervention, were implemented in 2 towns. Body weight, height, and waist circumferences were measured. Children recorded their dietary intake on a computer-based 24h recall. All children also completed validated computer based questionnaires to estimate physical activity, diet quality, eating behaviors, and quality of life and sleep. Additionally, parental diet quality and physical activity were assessed by validated questionnaires.

**Discussion:**

This study will provide insight in the efficacy of the THAO-Child Health Program to promote a healthy lifestyle. Additionally it will evaluate if lifestyle changes are accompanied by favorable weight management.

**Trial registration:**

Trial Registration Number ISRCTN68403446

## Background

Obesity can reverse the growing trend of life expectancy [1]. Adiposity is associated with an adverse cardiometabolic profile cardiovascular not only in adults but also in children [2]. In this context it is important to note that there is a high likelihood of tracking childhood obesity into adulthood [3].

The speeding growth of childhood overweight and obesity [4] is a serious problem for public health worldwide [5]. Spain has one of the highest prevalence rates of childhood overweight and obesity among OECD countries. A recent study reported prevalence rates of 25,3% and 9,6% of overweight and obesity, respectively, in Spanish children aged 8-13 years [6]. Childhood obesity has a multifactorial aetiology. Unhealthy lifestyle such as inadequate diet and low physical activity is strongly related with weight gain [7].

Community Based Interventions programs (CBI) are a holistic approach to prevent childhood obesity. CBI act from all key sectors that influence childhood development (family, school, health professionals, sports, media, shops and market). There is limit information on the efficacy of CBI in Europe. Results from the Fleurbaix Laventie Ville Santé (FLVS) study showed that the implementation of a CBI program resulted in less weight gain in the intervention towns compared with the control towns [8]. Based on these results the EPODE program started in 2004 in France.

The THAO-Child health program (TCHP) a community based intervention program is based on the EPODE methodology. The main objective of this program is to prevent childhood obesity by promoting healthy lifestyle among children and their families. The TCHP is implemented by municipalities with the political involvement of the Mayor-Councillors and other local project managers appointed by the Mayor or Councillors. The local project manager integrates all the key stakeholders involved actively in community life. The TCHP is currently implemented in 75 municipalities of 8 Spanish autonomous communities.

This manuscript describes the rational and design of the POIBC study aiming to determine the efficacy of the TCHP.

## Methods

### Study design

A parallel intervention study to determine the effect of the THAO-Child Health Program on weight management, physical activity, quality of life, diet and sleep quality, and habits and behaviours.

### Subjects

Two thousand two hundred forty nine children aged 8 to 10 years (4^th^ and 5^th^ grade of elementary school) were recruited from 4 Catalan cities (Terrassa, Sant Boi de Llobregat, Molins de Rei, and Gavà) from September to November 2012. The Thao-Child Health Program was implemented in Terrassa y Sant Boi de Llobregat whereas Molins de Rei and Gavà serve as control cities.

### Sample size calculation

The sample size calculation is based on data on 1 year changes in BMI of children from 14 towns where the THAO intervention program has been implemented. A decrease in BMI of 0.55 kg/m^2^ was observed. Therefore, we considered reasonable to assume a difference in BMI of 0,6 kg/m^2^ between control and intervention group. 1070 participants in each group are necessary to detect a difference in BMI of 0.6 kg/m^2^ or higher assuming a 0,05 alpha risk and 0,2 beta risk in a bilateral contrast. A BMI standard deviation of 4.43 kg/m^2^ was assumed and 20% of missing during follow up was estimated.

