### Statistic

Data clean-up will be performed to minimize errors. Linear multivariate mixed models will be fit to analyze differences in changes in quantitative variables between groups. Pre-post changes will be considered as the response variable, and participants’ (age, gender, etc.) and municipalities’ characteristics (group membership) will be included as fixed effects explanatory variables. Additionally, to account for the hierarchical structure of the data, municipalities (Terrassa, Sant Boi de Llobregat, Molins de Rei, and Gavà) will be added to the model as random effects factors.

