There is little data about the effect of CBI programs in European countries [28,29]. Therefore, it is paramount to develop and implement CBI programs tailored for country specific conditions in Europe. The POIBC study aims to determine the efficacy of the THAO-Child Health Program, a multisetting and multistrategy CBI program based on EPODE methodology [33]. The THAO-Child Health Program has been implemented in 75 towns in Spain since 2007. A basic characteristic of this program is the coordination by local authorities (municipalities) and the involvement of key sectors, such as schools, kindergarten, markets, sports and leisure time associations, health care providers and other local institutions relevant for child health. The TCHP includes health promotion materials and actions, permanent training of local coordinators and the development of an assessment and communication plan. This study represents an advance with respect to previously reported interventions in childhood obesity because the TCHP represents a sustainable intervention for municipalities and offers the possibility of maintain existing actions. Furthermore, the actions are carried out under the same communication model, and cartoon characters called “Thaoines” facilitate the health education of children. The TCHP is based on the I-Change Model defined by de Vries (last updated I-Change Model 2.0, 2008 [34]). This model is an amplification of the ASE model [Attitude – Social influence – self Efficacy Model [35]). The basic concept of the I-Change Model is an integration of ideas from Ajzen’s Theory of Planned Behaviour] [36], Bandura’s Social Cognitive Theory [37], Prochaska’s Transtheoretical Model [38], the Health Belief Model [39] and goal setting theories [40].

The POIBC study includes 2 intervention and 2 control towns and monitorate anthropometric variables and obesity related behaviour. Furthermore, parental socioeconomic status and lifestyle are recorded. An innovative aspect of the POIC study is the implementation of an on-line questionnaires to record lifestyle variables in children. Compared with the paper versions, the on-line software allows the children to answer in a more dynamic way. This, in turn, may help reduce mistakes in the response process.

A limitation of the POIBC study is its non-representative design. However, intervention and control towns have similar sociodemographic and socioeconomic characteristics, and are located in the same geographical area.

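### The 1070 per group allows nothing for clustering by town (2 v 2), so the stated 80% power holds only for independent children judged against a large-sample reference

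*Protocol article*

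**What the plan says.** The Sample size calculation section of the protocol article gives every input to its figure:

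- Effect: "we considered reasonable to assume a difference in BMI of 0,6 kg/m^2^ between control and intervention group".
- Error rates: "assuming a 0,05 alpha risk and 0,2 beta risk in a bilateral contrast".
- Spread: "A BMI standard deviation of 4.43 kg/m^2^ was assumed".
- Loss: "20% of missing during follow up was estimated".
- Result: "1070 participants in each group are necessary to detect a difference in BMI of 0.6 kg/m^2^ or higher".

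The section mentions no ICC and no design effect, and it does not use the number of study towns.

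The Subjects and Intervention sections name two towns that receive the programme and two that serve as controls. The Discussion repeats this: "The POIBC study includes 2 intervention and 2 control towns". The Statistic section makes pre-post change the response and enters group membership as a municipality characteristic. It then adds municipality as a random effect, a step it introduces with "Additionally, to account for the hierarchical structure of the data".

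**The concern.** The programme reaches every participating child in a town together, so group and town are completely confounded within each group. In the planned model, the group effect is a contrast between two towns and two other towns. Its standard error contains the between-town variance divided by the number of towns, and recruiting more children in the same towns does not reduce that part.

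The sample size paragraph prices a comparison of independent children, whereas the Statistic section plans a model that recognises towns. If the 80% is taken at face value, a reader of a non-significant result may give it more weight against the programme than the design can support.

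**Working it through.** **1. Reproduce the stated figure.** Inputs from the Sample size calculation section: difference 0.6, SD 4.43, two-sided alpha 0.05, power 0.80, loss 20%.

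n = 2 × (1.960 + 0.8416)² × 4.43² / 0.6² = 855.7, so 856 completers per group.

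856 / (1 − 0.20) = 1070.

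The match is exact. The loss adjustment accounts for the whole step from 856 to 1070, so the design effect used is 1.

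**2. Allow for towns.** With 2 towns per group and m analysed children per town,

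SE of the difference = SD × √[ICC + (1 − ICC)/m].

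The number recruited is 2249 (Subjects section). After 20% loss, 2249 × 0.8 / 4 = 449.8, taken as m = 450. Equal town sizes are an assumption, because no counts by town are given. The ICC is also an assumption, shown as a range. The design effect is 1 + 449 × ICC.

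Two references are used, since the Statistic section names none: the normal (critical value 1.960), and a noncentral t on 4 towns − 2 groups = 2 df (critical value 4.303). For 80% power, the difference divided by its SE must be 2.80 (normal) or 5.65 (2 df).

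Stated SD, 4.43:

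| Town ICC | Design effect | SE | Power, normal | Power, 2 df | Detectable difference at 80%, normal / 2 df | 95% CI half-width, normal / 2 df |
|---|---|---|---|---|---|---|
| 0 | 1 | 0.209 | 82% | 36% | 0.59 / 1.18 | 0.41 / 0.90 |
| 0.001 | 1.45 | 0.251 | 67% | 28% | 0.70 / 1.42 | 0.49 / 1.08 |
| 0.005 | 3.24 | 0.376 | 36% | 16% | 1.05 / 2.13 | 0.74 / 1.62 |
| 0.01 | 5.49 | 0.489 | 23% | 12% | 1.37 / 2.77 | 0.96 / 2.1 |

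(Differences and half-widths in kg/m². The 67% is 66.5% before rounding.)

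**3. Check the planned number itself.** With the 856 completers per group that the plan requires (428 per town), normal-reference power is 80.0%, 65%, 35% and 23% at the same four ICCs. On 2 df it is 35%, 27%, 16% and 12%. Recruiting 2249 instead of 2140 changes little: about 900 instead of 856 analysed per group offsets an ICC of (900/856 − 1)/449 ≈ 0.0001.

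**4. Could more children in these towns repair it?** As m grows without limit, the SE tends to SD × √ICC. Even with the normal reference, 80% power then needs ICC < [0.6 / (2.80 × 4.43)]² ≈ 0.0023.

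**5. Vary the SD.** The 4.43 is labelled an SD of BMI, but the response to be analysed is change in BMI. The documents give no SD of change. If the baseline to follow-up correlation were 0.9 (assumption), it would be 4.43 × √[2 × (1 − 0.9)] = 1.98, about 2.0. With SD 2.0 and m = 450:

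| Town ICC of change | Power, normal | Power, 2 df |
|---|---|---|
| 0 | 100% | 87% |
| 0.001 | 100% | 76% |
| 0.005 | 94% | 48% |
| 0.01 | 78% | 34% |

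**The case against.** The best reply has four parts.

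- **Degrees of freedom.** A reader might infer that the study lacks 80% power even when the town ICC is exactly zero. The documents do not support that as a flat statement. It follows only from a 2-df reference, which the Statistic section does not specify and which an article may leave to the full plan. With a normal reference and ICC 0, power is 82% and the claim is met. A 2-df reference is a reasonable choice with four towns, but it is an assumption here. This part of the reply stands.
- **SD.** A reader might take 12% to 36% as the study's power. That range combines the 2-df reference with an SD that does not describe the planned response. With a change SD near 2.0, power under the normal reference is 94% or more up to ICC 0.005 and 78% at 0.01. This also stands as a limit on the size of the loss. It does not rescue the printed calculation, which rests on 4.43.
- **The analysis does recognise clustering.** That is correct. The stated arithmetic is also right for the formula used. The defect is confined to the power statement, which omits a feature of the design that the analysis section takes into account.
- **No randomisation is described.** This is true but makes no difference, since assignment of the programme by town creates the dependence either way.

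**Conclusion.** The point holds in a limited form. The 1070 per group is the size for independent children. The 80% attached to it is valid only if children within a town are independent and the test uses a large-sample reference. Under the protocol's own SD, an ICC as small as 0.001 takes power below 80% with either reference (about 67% normal, 28% on 2 df), and at 0.01 it is about 23% or 12%.

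The direction of the error is firm: any positive town ICC lowers power below that of the independent-children calculation. The size is not firm. It depends on three quantities that the documents do not give: the town ICC, the SD of change and the reference distribution. It also assumes equal towns. If the change SD were about 2.0, power could be near or above 80% across the ICC range shown with a normal reference, but on 2 df it passes 80% only at ICC 0 among the values examined.

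**What to change.** Restate the Sample size calculation paragraph in three steps.

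1. Say that 1070 per group gives 80% power for 0.6 kg/m² only if children are independent.
2. Report power, detectable difference and expected confidence-interval half-width for two towns per group over a range of assumed town ICCs (for example 0, 0.001, 0.005 and 0.01). State the SD, the reference distribution and the town sizes as assumptions, and give results for the SD of change as well as for 4.43.
3. Use the 14-town programme data cited in that section to inform the ICC if child-level records are available, which the article does not show. Note that the programme was implemented in all those towns, so their variation may not represent control towns.

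The study should not be relabelled as sized for estimation, because the paragraph says that it was sized to detect 0.6 kg/m². No added enrolment is needed; recruitment ran from September to November 2012. The cost is one rewritten paragraph, a short calculation and, under the stated SD, a less favourable power statement.

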### Intervention

The THAO-Child Health Program is being implemented in Terrassa and Sant Boi de Llobregat, with Molins de Rei and Gavà acting as control cities. Repeated measures of dietary intake and behaviour, physical activity, sleep quality, quality of life, and anthropometric variables will be performed during 2 years among all participating children. Additionally, parental sociodemographic variables, diet quality, and physical activity will be recorded. Computer-based software and questionnaires have been developed to record children’s lifestyle habits.

The main objective of the THAO-Child Health Program is the prevention of childhood obesity through the promotion of healthy lifestyles of children and their families. THAO-Child Health Program it’s leaded by the city council which appoints the local coordinator who is supported by a multidisciplinary local team to reach all key sectors (family, school, health professionals, sports, media, shops and market). It’s a complete multisetting and multistrategy CBI.The Thao Foundation coordinate networks which develop the public health strategy, create the graphic materials and activities to all local key sectors. Furthermore, it gives the initial and the periodical training to local teams and coordinators and provides a constant support and annual evaluation to each town involved. All actions are being communicated by multiple channels (Figure 1).

**Figure 1 F1:**
[figure not shown]
THAO-Child health program implementation methodology in towns.

### Data collection in children

#### Anthropometric variables

Anthropometric measurements are assessed for each individual following standard protocol by trained personnel. Body weight, height, and waist circumferences were measured on the same day of the first interview with the subjects wearing a t-shirt and light trousers. The measurements are performed without shoes and using an electronic scale (SECA 813), to the nearest of 100 g, a portable SECA 213 stadiometer (to the nearest 1 mm), and a metric tape (to the nearest 1 mm). Using a flexible non-stretch tape measure, waist circumference was measured by trained interviewers in the narrowest zone between the lower costal rib and iliac crest, in the supine decubitus and horizontal positions. Measuring devices are systematically calibrated.

#### Online software

All lifestyle data are self-reported with the assistance of trained personnel. Dietary intake information based is collected by a new on-line program at each participant’s school. This program consists of a single and structured 24-h recall. Photographs were provided for all foods and beverages. Additionally, photographs of different portion sizes of most consumed foods of Spanish children aged 8 to 10 years are available.

The online program includes, beside the 24h recall, the following questionnaires

1. The KIDMED questionnaire [9]

2. The Dutch Eating Behaviour Questionnaire for Children (DEBQ-C) [10]

3. An eating habit questionnaire.

4. The Physical Activity Questionnaire for Children (PAQ-C) [11].

5. The KIDSCREEN-10 questionnaire [12]

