### Evaluation plan

The evaluation plan will be carried out during two scholar years. All variables will be collected in parents and children at the beginning of the 1^st^ scholar year and at the end of the 2^nd^ scholar year. An intermediate data collection at the beginning of the 2^nd^ scholar will be performed in children.

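### One school-based 24-h recall per wave cannot see Saturday and mixes Sundays with school days, so the intake-change models should carry recalled-day type

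*Protocol article*

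**What the plan says.** The Online software section of the protocol article fixes the place and the number of recalls: "Dietary intake information based is collected by a new on-line program at each participant’s school", and "This program consists of a single and structured 24-h recall". The recall is not the only diet measure, because "The online program includes, beside the 24h recall, the following questionnaires" introduces a list containing KIDMED and an eating habit questionnaire.

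The Evaluation plan sets three collections in children: "All variables will be collected in parents and children at the beginning of the 1^st^ scholar year and at the end of the 2^nd^ scholar" (that is, one at the start and one at the close of the study), plus "An intermediate data collection at the beginning of the 2^nd^ scholar will be performed in children". That gives one recall per wave and up to three per child.

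The Statistic section states that "Pre-post changes will be considered as the response variable". It names age, gender and group as fixed effects, in a list left open by an etc., and municipality as a random effect. Recall day is not named. The Discussion part of the abstract adds a further aim: "Additionally it will evaluate if lifestyle changes are accompanied by favorable weight management".

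The article does not give the weekday of the school visits. Nor does it say whether the recall refers to the previous calendar day or the last 24 hours.

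**The concern.** Two stated features, one recall per wave and a school setting, together decide which days of the week can be observed. A recall taken on a school day looks back one day only, so most weekend eating is out of reach. The Intervention section says the programme works through families, shops and markets as well as schools. An effect on Saturday eating would not show in the recall data.

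The second issue is the mix of days that are observed. A Monday session describes a Sunday and any other session describes a school day. When change is the response, a switch between these day types from one wave to the next enters the outcome as if intake had changed. With only two towns per arm, an uneven switch cannot be relied on to average out.

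At stake is the precision, and possibly the validity, of the between-arm contrast in quantitative intake. Also at stake is the use that can be made of single-day intake if diet change is related to weight change child by child.

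**Working it through.** **The plan's own figure.** The article gives no effect size, SD or sample size for intake. Its only sample size concerns BMI: 2 × (1.960 + 0.842)² × 4.43² / 0.6² ≈ 856 per group, and 856 / 0.8 = 1070, as stated. It reproduces and this point does not affect it.

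**Step 1: days covered.** Inputs: one recall, at school (Online software). Assumption: a Monday-to-Friday school week.

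| Session day | Previous-day recall covers |
|---|---|
| Monday | Sunday |
| Tuesday | Monday |
| Wednesday | Tuesday |
| Thursday | Wednesday |
| Friday | Thursday |

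Friday and Saturday have no chance of being sampled: 2/7 = 29% of the week. If the recall instead covers the last 24 hours, a Friday session picks up Friday until the session starts, but the rest of Friday and all of Saturday stay unobserved.

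**Step 2: effect on the change score.** Let D be mean Sunday intake minus mean school-day intake. A child moving from a school-day recall to a Sunday recall gains +D in the change score, the reverse move gives −D, and no switch gives 0.

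Noise: if visits are spread evenly over five days, the Sunday share is p = 0.2. With day type independent between waves, the added variance per child is 2p(1 − p)D² = 0.32 D², an SD of 0.57 D. For an assumed D of 100 to 200 kcal this is 57 to 113 kcal.

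Bias: let s be the pre-post shift in the Sunday share in the intervention arm minus that in the control arm. The spurious between-arm difference is D × s.

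| s | D = 100 kcal | D = 200 kcal |
|---|---|---|
| 0 | 0 | 0 |
| 0.1 | 10 | 20 |
| 0.2 | 20 | 40 |
| 0.5 | 50 | 100 |

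For example, s = 0.2 arises if the Sunday share rises from 0.20 to 0.30 in one arm and falls from 0.30 to 0.20 in the other. D and s are assumptions; the article supplies neither.

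**Step 3: use at child level.** Let λ be the within-child to between-child variance ratio of daily intake. One recall has reliability 1/(1 + λ) for usual intake. At an assumed λ of 1.5 this is 1/2.5 = 0.40; at λ = 2 it is 1/3 = 0.33. For a change between two single recalls, with usual intake correlated r between waves, reliability is (1 − r)/((1 − r) + λ). At an assumed r = 0.5 this is 0.5/2.0 = 0.25 and 0.5/2.5 = 0.20. A slope of weight change on recall-based intake change would then be attenuated to 20 to 25% of its true size. This applies only where intake is the predictor. Random error in intake as a response costs precision but does not shrink the group effect.

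**The case against.** The strongest reply is that this is a condensed article. Visit scheduling and the complete covariate list normally sit in a fuller protocol or analysis plan, and the list here is explicitly open. That is right: silence about the recall weekday is not an error. What remains is the coverage limit and the possible mixing of day types, which follow from what the article does state once an ordinary school week is assumed.

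Several stronger readings are tempting, and the document does not support them:

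- **That the arm contrast in intake is biased.** Nothing shows that the Sunday share shifts differently between arms. With the same shift in both, the bias is zero and only variance is added.
- **That omitting Friday and Saturday biases the measured change.** A constant omission narrows what the result describes. It does not bias change on the days observed.
- **That Friday is certainly lost, or that whole classes share a recalled day.** The first needs a previous-day window and the second needs sessions run class by class. The article states neither.
- **That diet as a whole rests on one day.** KIDMED and the eating habit questionnaire are separate from the recall.
- **That the planned analysis is attenuated.** The Statistic section compares change between groups. The abstract's aim of relating lifestyle change to weight does not commit the study to a child-level regression on recall intake.

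It is also fair to say that no scheduling or covariate remedy recovers Friday or Saturday. Only a narrower claim deals with that part.

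**Conclusion.** The point holds as a limited, inexpensive improvement to one outcome, quantitative intake. Given a Monday-to-Friday school week, Saturday is unobservable and Friday wholly or partly so (2 of 7 days with a previous-day recall). Sunday is seen only through Monday sessions. Changes of day type between waves add noise to the pre-post change. They bias the between-arm contrast only if the Sunday share shifts unequally: 0 kcal/day at s = 0, and 20 to 40 kcal/day at s = 0.2 with D of 100 to 200 kcal, all assumed values. The child-level caution is conditional on such an analysis being done and on the assumed variance ratio of 1.5 to 2.

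**What to change.** 1. In the intake-change models, include recalled-day type (Sunday v school day) at each wave as a fixed covariate. This needs the recall date per child. It works through variation in day type within towns, so it helps little if a town's recalls all fall on one day type.
2. Where scheduling allows, hold each school's recall at the two remaining child waves on the same weekday as at baseline. If this is achieved, D cancels from the change score and the covariate serves only for exceptions.
3. State that recall results describe the days covered, about Sunday to Thursday, and interpret them as group means.
4. If diet change is related to weight change at child level, name KIDMED as the main diet measure. It is already collected and is not tied to one recalled day.

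The cost is slightly less flexible school scheduling, one additional covariate per wave and a narrower claim for the recall. No extra recalls or staff are needed. If the later waves can no longer be rescheduled, items 1, 3 and 4 still apply.
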